**Revision history**

| **Version number**  **Date** | **Description** | **Date approved REC** |
| --- | --- | --- |
| 1.0  09.06.2020 | Original submission |  |
| 1.1  09.09.2020 | New version number and date  Change of data retention period from 10 to five years and total study period from 15 to 10 years. | 28.09.2020 |
| 1.2  01.02.2021 | New version number and date  Change in the text in **6.3 The primary endpoint.** Specification and detailed description are added  Change/specification in **7.2 Inclusion criteria**, removed “*Witnessed arrest or*” and “*Commenced*” from third and fourth inclusion criteria.  Change/specification in **7.3 Exclusion criteria**:   - Removed “*Age less than 18 years or above 80 years*” - Specified to “*Accidental hypothermia with temperature < 32 ^0^C”* - Added “*Suspected non-traumatic haemorrhage as aetiology of the arrest*”   Added “*Asphyxia as probable cause of arrest*” in **9.8 Specification of exploratory subgroups**  Edited **10.1 Randomisation procedure,** change from “*one randomised block*” to “*envelopes*”  Added cerebral oximetry equipment to **10.2.1 Medical devices in both groups** and **11.1.2 During treatment** | 11.02.2021 |
| 1.3  14.06.2021 | New version number and date  Change in text in **6.5 Exploratory endpoints**, to “*Incidence of all adverse events*” |  |

# Clinical study summary

**Title**: Resuscitative endovascular balloon occlusion of the aorta in non-traumatic out of hospital cardiac arrest – The REBOARREST Trial

**Study objectives**: The primary objective is to assess the efficacy of resuscitative endovascular balloon occlusion of the aorta (REBOA) as an adjunct treatment to advanced cardiovascular life support (ACLS) in patients with out-of-hospital cardiac arrest.

Secondary objectives are 1) to describe the hemodynamic physiology of aortic occlusion during ACLS, 2) a description of any adverse events and 3) description of 30-days survival.

**Clinical study design**: A prospective, randomised, parallel group, multi-centre, phase II clinical trial. Patients are randomised in a 1:1 ratio to be included to the control group or the intervention group. 200 patients will be included in the trial.

**Intervention and control**: The control group receives ACLS according to national guidelines.

The intervention group receives ACLS according to national guidelines and the REBOA procedure as an adjunct treatment.

**Inclusion criteria**: Age 18 to 80 years, out-of-hospital cardiac arrest, non-traumatic cardiac arrest, witnessed arrest or less than 10 minutes from debut of arrest to start of basic or advanced cardiac life support, commenced ACLS is established and can be continued.

**Exclusion criteria**: Age less than 18 or above 80 years, traumatic cardiac arrest, hypothermia, pregnancy, suspected cerebral haemorrhage as aetiology of the arrest, unable to perform ACLS as per national guideline, patient included to the study site’s E-CPR protocol, other factors as decided by the treatment team (environmental factors, safety factors and others).

**Primary endpoint**: The primary endpoint of this study is the proportion of patients that achieve return of spontaneous circulation (ROSC).

**Secondary endpoints**: -30-day survival rate with good neurologic status defined as modified Rankin scale (mRS) score 0-3.

-Difference in end-tidal CO2 measurements in the control group and the intervention group after aortic occlusion.

-Change in blood pressures after aortic occlusion.

-Difference in left ventricular ejection fraction measured by echocardiography

**Safety reporting**: -A three-step safety program will be conducted: 1) After each included patient, the physician will be interviewed by an investigator. 2) Ultrasound images from patients in the intervention group will be reviewed to ensure arterial catheter placement. 3) An external expert panel will perform a case review using all available information.

-Serious adverse events and serious adverse device events will be reported.

-An independent data monitoring committee will be established.

**Duration of study**: The trial period for each patient is one year after randomisation. The trial is expected to start winter 2020/2021. Inclusion of patients is estimated to take three years. Follow up and five-year data retention period necessitate a total study period of 10 year.

**Follow up**: Patient journal will be examined one year after randomisation to assess survival.

[1 Contact details 3](#_Toc42542846)

[1.1 Project management 4](#_Toc42542847)

[2 Signatures 5](#_Toc42542848)

[3 Clinical study summary 6](#_Toc42542849)

[4 Abbreviations 10](#_Toc42542850)

[5 Introduction 11](#_Toc42542851)

[5.1 Background 11](#_Toc42542852)

[5.1.1 Current knowledge and practice 11](#_Toc42542853)

[5.1.2 Other adjuncts to advanced cardiovascular life support 12](#_Toc42542854)

[5.1.3 Rationale for use and anticipated clinical benefits of REBOA 12](#_Toc42542855)

[5.1.4 Epidemiology of cardiac arrest 13](#_Toc42542856)

[5.2 Study Rationale 13](#_Toc42542857)

[5.3 Academic study 14](#_Toc42542858)

[6 Objectives and endpoints 14](#_Toc42542859)

[6.1 Primary objective of the study 14](#_Toc42542860)

[6.2 Secondary objective of the study 14](#_Toc42542861)

[6.3 The primary endpoint 14](#_Toc42542862)

[6.4 The secondary endpoints 14](#_Toc42542863)

[6.5 Exploratory endpoints 15](#_Toc42542864)

[7 Study population 15](#_Toc42542865)

[7.1 Selection of participants and study setting: 15](#_Toc42542866)

[7.2 Inclusion criteria 15](#_Toc42542867)

[7.3 Exclusion criteria 16](#_Toc42542868)

[7.4 Criteria for withdrawal or discontinuation 16](#_Toc42542869)

[7.5 Enrolment 16](#_Toc42542870)

[8 Informed consent process 16](#_Toc42542871)

[9 Statistics 17](#_Toc42542872)

[9.1 Statistical hypothesis 17](#_Toc42542873)

[9.2 Sample size 17](#_Toc42542874)

[9.3 Interim analyses 18](#_Toc42542875)

[9.4 Measures to minimize bias 19](#_Toc42542876)

[9.5 Statistical design 19](#_Toc42542877)

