## The secondary endpoints

1. 30-day survival rate with good neurologic status defined as modified Rankin scale (mRS) score 0-3.

We dichotomise the mRs into good (score 0-3) and poor (score 4-6) neurological state (appendix 29.2) to enable both binary statistical analysis and a reasonable clinical interpretation of trial results, as performed in other large cardiac arrest studies ^35^. The mRS is commonly used as a primary outcome scale for acute stroke trials ^36^, but is increasingly used also in cardiac arrest research and has been recommended in the International Liaison Committee on Resuscitation as part of the Utstein template ^37,38^. The outcome is also in accordance with recently published Core Outcome Set for Cardiac Arrest trials ^39^.

1. Difference in end-tidal CO2 measurements in the control group and the intervention group after aortic occlusion.

EtCO2 measurements is a proxy measurement of central circulation, shown feasible in this setting ^1^. This pilot study reported a significant increase in EtCO2 after 30, 60 and 90 seconds. This allows for comparison of the two groups, with a possible increase in central circulation as a hypothesized reason to an increased proportion of patients achieving ROSC. In the control group, EtCO2 is measured after airway management is completed. In the intervention group, EtCO2 is measured before balloon inflation and 30, 60 and 90 seconds after balloon inflation.

1. Change in blood pressures after aortic occlusion.

In the intervention group, intra-aortic blood pressure measurements from the REBOA catheter are recorded. This apply only to the catheters with CE/FDA approval for invasive blood pressure measurements and will therefore be assessed in a sub-group of the participants. Continuous registration of invasive blood pressure will start before aortic occlusion.

1. Left ventricular ejection fraction (LVEF) measured by echocardiography

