## Exploratory endpoints

1. All-cause mortality one year after randomization
2. Difference in organ function, using the Acute Kidney Injury Network (AKIN) classification, liver function blood tests and others.
3. Incidence of all adverse events

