## Laboratory Tests

Several blood samples are commonly drawn from patients admitted after OHCA. We will register results from these samples, both to address possible differences between the groups, but also to assess a potential visceral hypoperfusion in the intervention group, as discussed in chapter 13.

There will be no biobank established and all laboratory test in this trial will be performed in accordance with laboratory standard procedures.

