## Data collection during study period

Data will be registered according to this schedule.

[figure not shown]

These data points will be registered:

| **All patients** - data reported after randomisation | |
| --- | --- |
| Age |  |
| Gender |  |
| Habitus | *Cachectic, Normal, Adipose* |
| Location of the incident | *Public outdoors, public indoors, private indoors* |
| All concomitant medication and dose used |  |
| Route of administration | *Intravenous, intraosseous* |
| All relevant times | *DD.MM.YYYY: hh:mm* |
| Time of dispatch |  |
| Time of arrival |  |
| Time of randomisation |  |
| Cardiac rhythm at randomisation and fluctuations in rhythm during resuscitation | *VF, VT, PEA, AS* |
| Suspected aetiology of arrest | *cardiac, respiratory, intoxication/poisoning, non-traumatic haemorrhage* |
| Number of defibrillations | *n* |
| Compression machine used | *yes/no* |
| Airway management (main method) | *Supraglottic airway, Endotracheal intubation* |
| ROSC more than 20 minutes | *yes/no* |
| Data file from monitor used |  |

| **Control group - additional data** | |
| --- | --- |
| End-tidal CO2 measures after randomisation and after ROSC | *kPa* |
| Other relevant times | *DD.MM.YYYY hh:mm* |
| Time of ROSC |  |
| Time of departure from scene |  |
| Time of admission to hospital |  |

| **REBOA group - additional data** | |
| --- | --- |
| Space to perform procedure | *Good/acceptable, Challenging, Impossible* |
| Visibility/light conditions | *Good/acceptable, Challenging, Impossible* |
| Temperature | *Good/acceptable, Challenging, Impossible* |
| Wind/rain conditions | *Good/acceptable, Challenging, Impossible* |
| Available resources on the scene that were used | *Bystanders, Another doctor, Ambulance, Fire brigade* |
| Ultrasound image obtaining | *Good/acceptable, Challenging, Impossible* |
| Data file from ultrasound machine |  |
| Cannulation site | *Left, Right* |
| Numbers of cannulation attempts | *n* |
| End-tidal measures | *kPa* |
| Before and after inflation of balloon, and after ROSC |  |
| Palpable pulse in left radial artery | *yes/no* |
| before balloon inflation |  |
| after balloon inflation |  |
| Other relevant times | *DD.MM.YYYY hh:mm* |
| Time of balloon occlusion |  |
| Time of ROSC and deflation of the balloon |  |
| Time of departure from scene |  |
| Time of admission to hospital |  |

| **Delivered to hospital - additional data** | |
| --- | --- |
| Blood gas from admission |  |
| pH |  |
| pCO2 | *kPa* |

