| pO2 | *kPa* |
| SaO2 | *%* |
| Base Excess | *mmol/L* |
| HCO3 | *mmol/L* |
| s-Lactate | *mmol/L* |
| s-K | *mmol/L* |
| s-Na | *mmol/L* |
| s-Ca | *mmol/L* |
| Glucose | *mmol/L* |
| Blood sample analysis, up to 30 days, with time and date for samples | *DD.MM.YYY hh:mm* |
| White blood cells | *x10^3^/uL* |
| Blood platelets | *x10^3^/uL* |
| CRP | *mg/L* |
| Neuron Specific Enolase (NSE) after 48-72 h | *ug/L* |
| Troponins | *ng/L* |
| CK-MB and total-CK | *ug/L and U/L* |
| PT-INR |  |
| ASAT, ALAT | *U/L* |
| Bilirubin | *umol/L* |
| Albumin | *g/L* |
| Creatinine | *mmol/L* |
| Estimated GFR |  |
| Urine output, up to 30 days | *ml/day* |
| Complications related to REBOA equipment, with time and date for each complication | *yes/no, DD.MM.YYYY hh:mm* |
| Local haemorrhage requiring treatment |  |
| Lower limb ischemia |  |
| Infection requiring antibiotic treatment |  |
| Aortic dissection, rupture or injury |  |
| Femoral vessel dissection, rupture or injury |  |
| Surgical intervention/repair needed |  |
| Need for amputation  Other |  |
| Cardiac interventions  REBOA equipment used for in-hospital procedure | *PCI, IABP, IMPELLA, ECMO, other*  *Yes/no for each procedure* |
| Length of stay at intensive care unit during the 30-day period after randomisation | *number of days* |
| Length of stay in hospital during the 30-day period after randomisation | *number of days* |
| Length of invasive respiratory support during the 30-day period after randomisation | *number of days* |
| Length of renal replacement therapy dependency during the 30-day period after randomisation | *number of days* |
| Modified Rankin scale at day 30 | *0 to 6* |
| Survival one year after randomisation | *yes/no* |
| Results from radiologic exams first 30 days |  |
| Results from echocardiography first 30 days |  |
| Data from autopsy, if performed |  |

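### LVEF and organ function are framed as between-arm differences but are recorded only in patients delivered to hospital, an event REBOA is meant to increase, so a raw comparison may be biased

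*Protocol*

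**What the plan says.** Section 3 (Clinical study summary) gives the fourth secondary endpoint as "Difference in left ventricular ejection fraction measured by echocardiography". Section 6.4 (The secondary endpoints) gives it as "Left ventricular ejection fraction (LVEF) measured by echocardiography", without the word difference and without a time point, population or rule for patients who die. Section 6.5 (Exploratory endpoints) lists "Difference in organ function, using the Acute Kidney Injury Network (AKIN) classification, liver function blood tests and others".

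Section 12.2 (Data collection during study period) places the data for both under the block headed "Delivered to hospital - additional data". That block holds creatinine, estimated GFR, urine output, liver tests, days on renal replacement therapy and "Results from echocardiography first 30 days".

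Section 11.4 (Laboratory Tests) explains where the laboratory values come from: "Several blood samples are commonly drawn from patients admitted after OHCA". It says the results serve "both to address possible differences between the groups" and also to look for visceral hypoperfusion in the intervention group.

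Section 5.1.3 names more ROSC and more patients surviving to hospital as the potential benefit of REBOA. Section 9.2 sizes the trial on ROSC rising from 18% to 36%. Section 14.2 says every patient with sustained ROSC is taken to hospital, and section 13.1.4 expects some patients to be declared dead on scene.

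**The concern.** Randomisation balances the arms among everyone randomised. LVEF and organ function exist only in the subset that reaches hospital, and the trial's hypothesis is that REBOA enlarges that subset. If it does, the REBOA patients with values include some who would not have arrived under standard ACLS, and these have no counterpart among the controls with values. If they differ in cardiac or renal function, the arm means differ even when REBOA changes no patient's LVEF or kidney function.

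This matters because section 27 commits the main publication to the secondary endpoints, and section 11.4 gives the laboratory comparison a safety purpose. A raw difference could be read as organ harm from aortic occlusion when it is selection. Selection could equally hide real harm.

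The protocol avoids this problem for the neurological endpoint, because mRS scores death as 6 (section 6.4 and appendix 29.2). LVEF and organ function have no such rule. Section 9.9 mentions only possible multiple imputation, which does not suit a value that death makes undefined.

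**Working it through.** **The plan's own figure.** The only relevant number in the protocol is the ROSC sample size (section 9.2: 18% versus 36%, power 0.80, two-sided 0.05, 94 per group). The pooled two-proportion formula, with mean rate 0.27, gives

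n = [1.96 × √(2 × 0.27 × 0.73) + 0.842 × √(0.18 × 0.82 + 0.36 × 0.64)]² / 0.18² ≈ 94.3.

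The stated 94 is reproduced (95 if rounded up). The planned size is 100 per arm. The protocol gives no figure for LVEF or organ function.

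**Who can be measured.** Using the ROSC rates as a proxy for hospital arrival, about 18 of 100 controls and 36 of 100 REBOA patients could have a value. The remaining 82 and 64 would not.

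**Share of extra arrivals.** Assume REBOA prevents no arrivals. With REBOA rate p, the share of measured REBOA patients who would not have arrived under control is (p - 0.18)/p. At p = 0.36 this is 18/36 = 50%.

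**Spurious difference.** Assume no effect of REBOA on any patient's LVEF, and extra arrivals whose LVEF is g points lower. The expected difference between arm means is then -g × (p - 0.18)/p.

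| REBOA rate | Extra share | g = 3 | g = 5 | g = 10 |
|---|---|---|---|---|
| 18% | 0% | 0 | 0 | 0 |
| 24% | 25% | -0.75 | -1.25 | -2.5 |
| 27% | 33% | -1.0 | -1.67 | -3.33 |
| 30% | 40% | -1.2 | -2.0 | -4.0 |
| 36% | 50% | -1.5 | -2.5 | -5.0 |

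**If a 5% test were run.** Assume SD 12 in each arm. SE = 12 × √(1/18 + 1/36) = 3.46.

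- g = 5: 2.5/3.46 = 0.72, so rejection probability is about 0.11.
- g = 10: 5/3.46 = 1.44, so rejection probability is about 0.30.

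A simulation of 20,000 trials with 100 per arm, random numbers arriving, Welch t-tests and the added spread from mixing two kinds of patient gave 10.8% and 27.6%. With g = 0 it gave 5.2%, which is the nominal level within simulation error.

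The gap g and the SD of 12 are assumptions; the protocol gives neither. The sign is also assumed: if the extra arrivals had better LVEF, the spurious difference would be positive.

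**The case against.** The strongest reply is that the protocol specifies no between-arm test for either outcome. Section 9.5 reserves hypothesis testing for the primary and other dichotomous secondary endpoints, and names regression only for end-tidal CO2 and blood pressure. Section 6.4 drops the word difference for LVEF. The summary is visibly not updated: it still carries an age exclusion and a witnessed-arrest criterion that sections 7.2 and 7.3 no longer contain. The secondary objectives are largely descriptive, organ function is labelled exploratory, and section 9 promises a separate SAP that could set the analysis population and the handling of death.

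Much of this stands. The absence of a detailed method is not a finding, and the rejection rates above show what a test would do, not what the protocol commits to. But the framing does not rest on the summary alone: section 6.5 also says difference, and section 11.4 says the laboratory results will address group differences. The stated descriptive objective concerns physiology during ACLS, which in-hospital echocardiography within 30 days is not. No section limits either outcome to description among those measured.

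Stronger readings are tempting, but the documents do not support them:

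- **The comparison is certainly biased, or biased against REBOA.** Bias needs REBOA to change who arrives and the extra arrivals to differ. The protocol hopes for the first and does not quantify the second. Section 9.6 also allows that REBOA may reduce good outcomes.
- **Survival is expected to double.** Only ROSC is planned to rise from 18% to 36%, as a sample-size assumption. Section 5.1.3 treats better 30-day survival as merely possible.
- **The measured set is patients who arrive alive.** Section 13.1.3 allows CPR to continue during transport, so the set is those delivered to hospital, and the ROSC rates only approximate it.
- **False rejection exceeds one half.** This needs a 15-point gap. Even then the rate is about 0.53 once the REBOA-arm SD is widened to √(12² + 7.5²) ≈ 14.1, and nothing in the protocol supports a gap of that size.

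**Conclusion.** The point holds as a defect in how the two endpoints are framed. Both are worded as between-arm contrasts, both are collected only after a post-randomisation event that REBOA is intended to make more common, and nothing elsewhere in the protocol repairs this. A raw difference would not be protected by randomisation and may be biased, in unknown direction and size.

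At the full planning effect, with extra arrivals 3 to 10 points lower, the spurious LVEF difference is -1.5 to -5.0 points. With REBOA ROSC rates of 24% to 30% and a 5-point gap it is -1.25 to -2.0 points. It is zero if there is no gap or no effect on arrival. These figures rest on an assumed gap, on ROSC as a proxy for arrival, on every arrival having a measurement and on REBOA preventing no arrivals. The rejection rates rest also on an SD of 12.

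The primary endpoint and the mRS endpoint are unaffected. The point carries more weight for LVEF, a secondary endpoint, than for organ function, an exploratory one.

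**What to change.** In sections 3, 6.4 and 6.5, state that LVEF and organ function are described by arm among patients delivered to hospital. For LVEF, use the first available echocardiogram after admission from the results already collected. Show per arm, next to each summary, the number not measured and the number dead. State that no between-arm test, efficacy claim or harm claim will be based on either outcome. Align the sentence in section 11.4 about group differences with this.

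A composite over all randomised patients with death ranked worst is at most an optional sensitivity analysis. At the planning rates about 82 control and 64 REBOA patients would have no value, most of them tied at the worst rank, so it would mostly reflect ROSC and survival and say little about LVEF.

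The cost is a wording amendment plus a rule for which recorded echocardiogram counts; no new measurement is needed. The downside is giving up a p-value for these two endpoints.

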# Abbreviations

ACLS Advanced Cardiovascular Life Support

ADE Adverse Device Effects

AE Adverse Event

CA Cardiac Arrest

CPR Cardiopulmonary Resuscitation

CRF Case Report Form

DMC Data monitoring committee

ECMO Extra-Corporeal Membrane Oxygenation

E-CPR Extracorporeal Cardiopulmonary Resuscitation

EtCO2 End Tidal CO2

HEMS Helicopter Emergency Medical Services

LVEF Left Ventricular Ejection Fraction

mRS Modified Rankin Scale

OHCA Out of Hospital Cardiac Arrest

PCI Percutaneous Coronary Intervention

P-EMS Physician-staffed Emergency Medical Services

REBOA Resuscitative Endovascular Balloon Occlusion of the Aorta

REC Regional Ethics Committee

ROSC Return of Spontaneous Circulation

SADE Serious Adverse Device Effect

SAE Serious Adverse Event

SI Site Investigator and/or designee

SPIRIT Standard Protocol Items: Recommendations for Interventional Trials

USADE Unanticipated Serious Adverse Device Effect

# Introduction

This is a randomised, parallel group, multi-centre, phase II clinical trial designed to assess the efficacy and hemodynamic effect of resuscitative endovascular balloon occlusion of the aorta (REBOA) in study subjects suffering from non-traumatic out of hospital cardiac arrest (OHCA).

200 patients will be enrolled in this study, 100 patients in each group.

This is the first prospective trial in the world to assess the efficacy of REBOA in non-traumatic cardiac arrest. The intervention is shown feasible in the pre-hospital setting^1^. If this trial provides a signal of benefit in patients, this study could initiate further clinical research which could change current resuscitation practice world-wide.

This is a multi-centre trial, with centres being consecutively recruited. Centres may include helicopter and/or rapid response car. Identified potentially centres are:

- Norwegian Air Ambulance base at Rosten, Trondheim, Norway.
- Rescue Helicopter Service at Ørland Main Airforce base, Brekstad, Norway.
- Norwegian Air Ambulance base in Bergen, Norway.
- Department of Air Ambulance Services, Prehospital Division, Oslo University Hospital, Norway.

Additional study sites may be eligible later.

This protocol is designed according to the Standard Protocol Items: Recommendations for Interventional Trials (SPIRIT) 2013 guidelines (appendix 29.1) and will be reported according to the Consolidated Standards Of Reporting Trials 2010 Guidelines ^2,3^.

